## Section 5: Trial population

### 21. Screening data

All intubation episodes in both centres will be assessed for eligibility for inclusion in the trial. The CONSORT flow diagram in Fig. 1 will be used to detail enrolment, randomisation, treatment allocation, follow-up, and analysis.

**Fig. 1 Fig1:**
[figure not shown]
Consolidated Standards of Reporting Trials (CONSORT) 2010 flow diagram

### 22. Eligibility criteria

Any patient undergoing endotracheal intubation in the DR or NICU is eligible for inclusion. Specific inclusion and exclusion criteria are outlined in the protocol [2].

### 23. CONSORT diagram

Please see Fig. 1.

### 24. Withdrawal/follow-up

Infants where prospective consent is withdrawn, or retrospective consent is not gained, will be treated as post-randomisation exclusions (Fig. 1).

### 25. Baseline patient characteristics at randomisation

The following baseline characteristics will be summarised (see Table 1):
Mothers:Mode of delivery: vaginal delivery, caesarean section under spinal anaesthesia, caesarean section under general anaesthesia: number (%)Infants:Gestational age (weeks): mean (standard deviation, SD)Birth weight (grams): mean (SD)Age at randomisation (hours): mean (SD)Corrected gestational age at randomisation (weeks): mean (SD)Weight at randomisation (grams): mean (SD)Male: number (%)Multiple birth: number (%)Apgar score at 5 min: median (interquartile range)Respiratory support prior to randomisation (no support, nHF, continuous positive airway pressure, intermittent positive pressure ventilation): number (%)Fraction of inspired oxygen prior to randomisation: (mean, SD)

**Table 1 Tab1:** Baseline characteristics at time of randomisation

Characteristic	Nasal HF group (*n =* XXX)	Control group (*n =* XXX)
Mothers		
Mode of delivery—no. (%)		
Vaginal delivery	XX (%)	XX (%)
Caesarean section under spinal anaesthesia	XX (%)	XX (%)
Caesarean section under general anaesthesia	XX (%)	XX (%)
Infants		
Gestational age at birth—weeks	Mean (SD)	Mean (SD)
≤ 28 weeks	XX (%)	XX (%)
> 28 weeks	XX (%)	XX (%)
Birth weight—grams	Mean (SD)	Mean (SD)
Age at randomisation—hours	Mean (SD)	Mean (SD)
Corrected GA at randomisation—weeks	Mean (SD)	Mean (SD)
Weight at randomisation—grams	Mean (SD)	Mean (SD)
Male—no. (%)	XX (%)	XX (%)
Multiple birth—no. (%)	XX (%)	XX (%)
Apgar score at 5 min	Mean (SD)	Mean (SD)
Respiratory support prior to randomisation		
Nasal high flow	XX (%)	XX (%)
Continuous positive airway pressure	XX (%)	XX (%)
Intermittent positive pressure ventilation (IPPV) (via face mask, does not include IPPV following premedication)	XX (%)	XX (%)
IPPV via endotracheal tube	XX (%)	XX (%)
Low flow oxygen	XX (%)	XX (%)
No respiratory support	XX (%)	XX (%)
Fraction of inspired oxygen prior to randomisation	Mean (SD)	Mean (SD)
**Intubation characteristic**		
Primary reason for intubation—no. (%)		
Hypoxia	XX (%)	XX (%)
Hypercarbia	XX (%)	XX (%)
Apnoea	XX (%)	XX (%)
Resuscitation	XX (%)	XX (%)
Other	XX (%)	XX (%)
Use of premedication—no. (%)		
Premedication	XX (%)	XX (%)
No premedication	XX (%)	XX (%)
First intubation attempt operator—no. (%)		
Resident/registrar/neonatal nurse practitioner	XX (%)	XX (%)
Fellow/consultant	XX (%)	XX (%)
Experience of operator (number of previous intubations)—no. (%)		
< 20 previous intubations	XX (%)	XX (%)
≥ 20 previous intubations	XX (%)	XX (%)

N.B. Baseline demographic characteristics are for all intubation episodes

## Section 6: Analysis

### 26. Outcome definitions

For all incidence outcomes, incidence is the proportion of first intubation attempts in which that outcome occurred.

#### Primary outcome

The primary outcome is incidence of successful intubation at the first attempt without physiological instability, i.e. the proportion of first intubation attempts in which successful intubation without physiological instability occurs (Table 2).

**Table 2 Tab2:** Primary outcome and components

Outcome	Nasal HF group (*n =* XXX)	Control group (*n =* XXX)	Risk difference (95% CI)
Intention-to-treat analysis			
Successful first attempt intubation without physiological instability	XX (%)	XX (%)	
≤ 28 weeks’ GA	XX (%)	XX (%)	
> 28 weeks’ GA	XX (%)	XX (%)	
Premedication use	XX (%)	XX (%)	
No premedication use	XX (%)	XX (%)	
Inexperienced operator (< 20 previous intubations	XX (%)	XX (%)	
Experienced operator (≥ 20 previous intubations)	XX (%)	XX (%)	
Successful first attempt intubation	XX (%)	XX (%)	
Desaturation (SpO_2_ > 20% from baseline) during the first intubation attempt	XX (%)	XX (%)	
Bradycardia (HR < 100 bpm) during the first intubation attempt	XX (%)	XX (%)	

#### Definitions

Intubation attempt: the insertion of the laryngoscope blade beyond the infant’s lips.Intubation duration: the time from the insertion of the laryngoscope blade beyond the infant’s lips until the removal of the laryngoscope blade from the infant’s mouth.Successful intubation: the completion of the intubation attempt with correct positioning of the endotracheal tube confirmed by detection of expired carbon dioxide on a colorimetric detector.Physiological instability: the incidence (any duration) of an absolute decrease in peripheral oxygen saturation (SpO_2_) > 20% from baseline (immediately prior to the intubation attempt), and/or bradycardia (heart rate < 100 beats per minute, bpm), during the first intubation attempt.

#### Secondary outcomes

Incidence of successful intubation on the first intubation attempt.Incidence of desaturation (absolute decrease in SpO_2_ > 20% from baseline) *or* bradycardia (heart rate < 100 bpm) during the first intubation attempt.In first intubation attempts where desaturation (absolute decrease in SpO_2_ > 20% from baseline) occurs, time to desaturation during the first intubation attempt in seconds.In first intubation attempts where bradycardia (heart rate < 100 bpm) occurs, time to bradycardia during the first intubation attempt in seconds.In first intubation attempts where desaturation (absolute decrease in SpO_2_ > 20% from baseline) occurs, duration of desaturation during first intubation attempt in seconds.In first intubation attempts where bradycardia (heart rate < 100 bpm) occurs, duration of bradycardia during first intubation attempt in seconds.Median SpO_2_ during first intubation attempt.Median heart rate during first intubation attempt.In first intubation attempts where SpO_2_ > 97% occurs, duration of SpO_2_ > 97% during first intubation attempt, in seconds.Number of intubation attempts.Duration of all intubation attempts (successful and unsuccessful), in seconds.Incidence of cardiac compressions and/or adrenaline administration within 1 h after the first intubation attempt.Incidence of pneumothorax within 72 h after randomisation, diagnosed either by transillumination of the chest and/or by chest X-ray.Incidence of pneumothorax requiring drainage (via needle thoracocentesis or insertion of an intercostal catheter) within 72 h after randomisation.Death within 72 h after randomisation.

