### 27. Analysis methods

For all outcomes, the difference between the 2 treatment groups will be estimated using multivariable regression, with the outcome as the dependent variable, the group allocation as the predictor, and the stratification factors used during randomisation (gestational age group, premedication use and trial centre) as covariates.

For binary outcome variables, including the primary outcome, the number and percentage of intubation attempts with the outcome will be presented separately for the 2 treatment groups. Binary regression (fitting a generalised linear model) will be used to estimate the difference between the treatment groups. The results will be reported as the difference in risk between the 2 treatment groups, with the 95% CI for the risk difference.

For continuous outcomes, the distribution of each outcome will be assessed visually using graphical methods (histogram and dotplot). If the distribution is considered to be so skewed that the mean is an inappropriate summary measure, the outcome will be summarised using the median, otherwise the outcome will be summarised by the mean.

Where the summary measure is the mean, the mean and SD will be presented separately for the 2 treatment groups. Linear regression will be used to estimate the difference between the treatment groups. The results will be reported as the difference of means between the 2 treatment groups, with the 95% CI for the difference of means.

Where the summary measure is the median, the median and IQR will be presented separately for the 2 treatment groups. Quantile regression will be used to estimate the difference between the treatment groups. The results will be reported as the difference of medians between the 2 treatment groups, with the 95% CI for the difference of medians.

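### Five secondary time and duration outcomes are compared between arms only among first attempts in which the event occurred, so randomisation does not protect these comparisons and they can mislead

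*SAP article*

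**What the plan says.** Section 26 (Secondary outcomes) defines five outcomes only for first attempts in which the event happened:

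- for desaturation: "occurs, time to desaturation during the first intubation attempt in seconds" and "occurs, duration of desaturation during first intubation attempt in seconds";
- for bradycardia: "occurs, time to bradycardia during the first intubation attempt in seconds" and "occurs, duration of bradycardia during first intubation attempt in seconds";
- for high saturation, duration alone: "In first intubation attempts where SpO_2_ > 97% occurs, duration of SpO_2_ > 97% during first intubation attempt, in seconds".

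Section 27 makes these comparative outcomes: "For all outcomes, the difference between the 2 treatment groups will be estimated using multivariable regression", with allocation and the stratification factors in the model. If the mean is the summary, "Linear regression will be used to estimate the difference between the treatment groups"; if the median is the summary, "Quantile regression will be used to estimate the difference between the treatment groups". Both come with a 95% CI. Section 12 places the secondary outcomes in a superiority framework, and Table 3 has a between-group difference column for the desaturation and bradycardia times and durations.

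The SAP plans no version of these five outcomes over all first attempts and gives no caveat on their interpretation. It does report the incidence of desaturation and of bradycardia over all first attempts (Table 2). For SpO2 above 97%, no incidence is listed and Table 3 has no row.

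**The concern.** Whether an infant desaturates or becomes bradycardic during the first attempt is known only after randomisation, and both events are part of the primary composite that nHF is being tested to improve. If nHF prevents some events, the nHF subset with events is no longer the counterpart of the control subset with events. It holds the infants whom nHF did not protect. Covariates for centre, age group and premedication cannot restore the balance, because the relevant difference is each infant's own tendency to desaturate early or late.

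The infants for whom nHF worked best, those who never desaturated, drop out of the comparison. This matters most for time to desaturation, the outcome closest to the background argument in Section 7 that high flow extends safe apnoea time in adults. If nHF mainly prevents late, mild events, the remaining nHF events are the early, long ones, and nHF can appear to bring desaturation forward and prolong it.

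**Working it through.** **The plan's own figures.** The SAP states no expected time or duration for these outcomes, so there is no figure of its own to reproduce. The only number taken from it is 123 episodes per arm. The usual pooled formula for 30% versus 50%, two-sided 0.05 and 90% power gives 124 per arm, and 123 per arm has 89.8% power, so the sample size is not in question.

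**Hand example (all inputs assumed), per 100 first attempts in each arm.** Severe desaturation: onset 15 s, lasting 40 s, 20 in each arm. Mild desaturation: onset 40 s, lasting 10 s, 30 in control and 10 with nHF. nHF prevents 20 mild events and harms nobody.

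- Mean duration among events: control (30×10 + 20×40)/50 = 22.0 s; nHF (10×10 + 20×40)/30 = 30.0 s.
- Mean onset among events: control (30×40 + 20×15)/50 = 30.0 s; nHF (10×40 + 20×15)/30 = 23.3 s.
- Mean duration over all attempts, 0 s if no event: control 1,100/100 = 11.0 s; nHF 900/100 = 9.0 s.

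The planned comparison makes nHF look worse on both outcomes; over all attempts it is better.

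**Simulation (all inputs assumed).** Attempt length D is lognormal with median 45 s and log-SD 0.5. Latent time to desaturation T is lognormal with median 40 s and log-SD 0.6, independent of D. Desaturation occurs if T < D; its duration is then D − T, otherwise 0. Late desaturators are infants with T above 40 s. No scenario harms any infant. Each used 4,000,000 episodes. Differences are nHF minus control, taken before rounding, so they may differ by 0.1 s from the rounded columns.

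| Scenario | Desaturation | Mean onset among events | Difference | Median onset among events | Mean duration among events | Mean duration, all attempts | Difference |
|---|---|---|---|---|---|---|---|
| Control | 56% | 32.3 s | | 29.4 s | 29.7 s | 16.6 s | |
| nHF protects all late desaturators | 42% | 25.1 s | -7.2 s | 25.1 s | 31.2 s | 13.0 s | -3.6 s |
| nHF protects half of them | 49% | 29.2 s | -3.1 s | 27.2 s | 30.3 s | 14.8 s | -1.8 s |
| nHF protects a random 40% of infants | 34% | 32.3 s | 0.0 s | 29.4 s | 29.7 s | 10.0 s | -6.7 s |
| nHF multiplies T by 1.25 | 45% | 37.0 s | +4.6 s | 33.7 s | 28.5 s | 12.7 s | -3.9 s |
| nHF multiplies T by 1.5 | 36% | 41.0 s | +8.7 s | 37.5 s | 27.8 s | 9.9 s | -6.7 s |

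The medians move in the same directions as the means, so choosing quantile regression does not avoid the problem. With 123 per arm, the 95% CI for mean onset lies wholly on the wrong side of zero in roughly nine trials in ten in the first nHF scenario, in about 22% in the second, and in 0.1% or fewer under proportional delay.

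**A second model (also assumed).** Attempt median 50 s; 40% frail infants with latent median 20 s and 60% robust infants with 45 s. If nHF doubles the time in robust infants only, median onset among events goes from 26.8 s to 22.0 s and mean duration among events from 32.4 s to 34.0 s, while mean duration over all attempts falls from 23.2 s to 16.1 s. A uniform delay of 1.5 times gives the right direction: median onset 33.9 s, mean duration among events 29.3 s.

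Bradycardia and SpO2 above 97% were not simulated; for them the argument is structural.

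**The case against.** **The worst case should not be the headline.** The -7 s result needs a sharp cut-off: nHF protects everyone who would desaturate after 40 s and nobody before. Protecting half of that group gives -3 s, and a proportional delay, arguably the closest reading of longer safe apnoea time, gives the correct direction. This stands. A reader might infer that the planned analysis will reverse the effect of nHF; the documents give no event times and do not support that.

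**A zero difference under random protection is not a bias.** It correctly describes infants who still desaturate, and the benefit appears in incidence. This also stands. The difficulty is that a reader of the trial report could not tell which scenario applied.

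**Whole-population effects are reported elsewhere.** Table 2 gives desaturation and bradycardia incidence with risk differences, and median SpO2 and heart rate carry no event restriction. This lowers the stakes, but it does not make the conditional differences valid, and SpO2 above 97% has no incidence beside it.

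**The consequences are limited.** These are secondary outcomes, reported under Section 17 as estimates with unadjusted CIs, and the restriction is written openly into each definition. That is right, and a reader should not infer any threat to the primary result. Nor does the SAP define a time to SpO2 above 97%, or say that nHF is meant to change that event.

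**The remedy has its own assumptions.** Attempts may be stopped because the infant is deteriorating, so treating the end of the attempt as ordinary censoring would be informative. Filling in zeros changes the estimand. Both points stand and shape the fix.

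**Conclusion.** The point holds and should be fixed, though it is not critical. Five secondary outcomes are compared between arms within subsets selected by a post-randomisation event, without protection from randomisation and without an all-attempts counterpart. Under the assumed event times, the among-events difference in mean onset of desaturation ranges from about -7 s through -3 s and 0 s to between +5 and +9 s, although in every scenario nHF harms no infant and reduces mean desaturation time over all attempts by about 2 to 7 s. The sign and size of the planned contrast therefore depend on which infants nHF helps, and the contrast alone cannot show that. Reversal is possible, not inevitable. These sizes rest wholly on assumed distributions; the structural point does not. The primary outcome, its analysis and the sample size are untouched.

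**What to change.** Make the between-arm comparison over all analysed first attempts.

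- **Three durations (desaturation, bradycardia, SpO2 above 97%):** assign 0 s to attempts observed to be free of the event, and compare means, adjusted for the stratification factors, with robust or bootstrap 95% CIs. Attempts with lost signal or failed video stay missing under Section 28; they are not zeros.
- **Time to desaturation and time to bradycardia:** report cumulative incidence from laryngoscope insertion, with the end of the attempt as a competing event and not as non-informative censoring. Fix in advance the times at which the arms are compared.
- **Among-events times and durations:** keep them as description by arm, without a between-group CI.

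The cost is a few sentences in Sections 26 and 27, changes to Table 3 and a little code. Section 14 already has every video reviewed for the secondary outcomes. The downside is that the durations become zero-inflated means that combine how often the event occurs with how long it lasts, which is why the descriptive figures should be kept beside them.

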### 27. Analysis methods

For all outcomes, the difference between the 2 treatment groups will be estimated using multivariable regression, with the outcome as the dependent variable, the group allocation as the predictor, and the stratification factors used during randomisation (gestational age group, premedication use and trial centre) as covariates.

For binary outcome variables, including the primary outcome, the number and percentage of intubation attempts with the outcome will be presented separately for the 2 treatment groups. Binary regression (fitting a generalised linear model) will be used to estimate the difference between the treatment groups. The results will be reported as the difference in risk between the 2 treatment groups, with the 95% CI for the risk difference.

For continuous outcomes, the distribution of each outcome will be assessed visually using graphical methods (histogram and dotplot). If the distribution is considered to be so skewed that the mean is an inappropriate summary measure, the outcome will be summarised using the median, otherwise the outcome will be summarised by the mean.

Where the summary measure is the mean, the mean and SD will be presented separately for the 2 treatment groups. Linear regression will be used to estimate the difference between the treatment groups. The results will be reported as the difference of means between the 2 treatment groups, with the 95% CI for the difference of means.

Where the summary measure is the median, the median and IQR will be presented separately for the 2 treatment groups. Quantile regression will be used to estimate the difference between the treatment groups. The results will be reported as the difference of medians between the 2 treatment groups, with the 95% CI for the difference of medians.

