#### Primary outcome—sensitivity analyses

As some infants will be randomised more than once, the difference in risk of the primary outcome between the 2 treatment groups, with the 95% CI for the risk difference, adjusted for repeated measures, will also be reported. The model used for this analysis will be a multivariable binary regression as described above, with standard errors estimated allowing for intragroup correlation (using the vce(cluster) option in Stata).

If an imbalance in demographics known to affect intubation success (e.g. postmenstrual age, weight, videolaryngoscope use, operator experience) is detected, a further sensitivity analysis adjusting for the relevant demographics will be conducted for the primary outcome.

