#### Analyses: secondary outcomes

Secondary outcomes will be analysed as described above. The results will be presented as outlined in Tables 3 and 1 (components of the primary outcome).

**Table 3 Tab3:** Secondary outcomes

Outcome	Nasal HF group (*n =* XXX)	Control group (*n =* XXX)	Risk difference or difference of means or difference of medians (95% CI)
Time to desaturation—seconds^a^	Mean (SD) or median (IQR)	Mean (SD) or median (IQR)	
Duration of desaturation—seconds^a^	Mean (SD) or median (IQR)	Mean (SD) or median (IQR)	
Median SpO_2_^a^	Mean (SD) or median (IQR)	Mean (SD) or median (IQR)	
Bradycardia (HR < 100 bpm)^a^	XX (%)	XX (%)	
Time to bradycardia—seconds^a^	Mean (SD) or median (IQR)	Mean (SD) or median (IQR)	
Duration of bradycardia—seconds^a^	Mean (SD) or median (IQR)	Mean (SD) or median (IQR)	
Median HR^a^	Mean (SD) or median (IQR)	Mean (SD) or median (IQR)	
Number of intubation attempts	Mean (SD) or median (IQR)	Mean (SD) or median (IQR)	
Total duration of all intubation attempts (successful and unsuccessful)—seconds^c^	Mean (SD) or median (IQR)	Mean (SD) or median (IQR)	
CPR and/or adrenaline administration within 1 h of intubation attempt^b^	XX (%)	XX (%)	
Pneumothorax diagnosed within 72 h after randomisation^b^	XX (%)	XX (%)	
Any	XX (%)	XX (%)	
Requiring drainage with needle thoracocentesis or intercostal catheter	XX (%)	XX (%)	
Death within 72 h after randomisation^b^	XX (%)	XX (%)	

^a^During first intubation attempt

^b^Specified as serious adverse events in trial

^c^Sum of each separate intubation attempt

*IQR* interquartile range, *SpO*_*2*_ peripheral oxygen saturation, *HR* heart rate, *Bpm* beats per minute, *CPR* cardiopulmonary resuscitation

There will be no subgroup analyses performed for secondary outcomes.

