### 28. Missing data

Every attempt will be undertaken to retrieve missing data. The primary outcome is recorded on a paper CRF by the investigator at the cot-side, to provide a backup to the video recording and time stamped downloadable oximetry recording. We therefore expect there to be very few instances in which the primary outcome cannot be determined and therefore do not anticipate needing to use multiple imputation to deal with missing data. Imputation will not be used for missing physiological data, for example in the event of loss of pulse oximetry signal or failure of video recording.

Multiple imputation or inverse probability case weights may be used to deal with missing data.

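### Median SpO2 and median heart rate during the first attempt are compared without adjusting for the pre-attempt value: a valid analysis that gives up precision and leaves a chance baseline imbalance unseen

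*SAP article*

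**What the plan says.** Section 27 (Analysis methods) sets one rule: "For all outcomes, the difference between the 2 treatment groups will be estimated using multivariable regression". The model has group allocation as predictor and "the stratification factors used during randomisation (gestational age group, premedication use and trial centre) as covariates". Under Analyses: secondary outcomes the same model is carried over: "Secondary outcomes will be analysed as described above".

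Two of the listed secondary outcomes are "Median SpO_2_ during first intubation attempt" and "Median heart rate during first intubation attempt". Both are levels, not changes. They go into linear regression, or into quantile regression if the distribution is judged too skewed.

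The Definitions in Section 26 score desaturation as a fall in SpO2 "from baseline (immediately prior to the intubation attempt"). Section 28 (Missing data) mentions a "time stamped downloadable oximetry recording", and Section 14 says that the oximeter is filmed.

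The only further covariate adjustment is conditional on an observed imbalance: "a further sensitivity analysis adjusting for the relevant demographics will be conducted for the primary outcome". It does not reach the secondary outcomes. Table 1 lists fraction of inspired oxygen before randomisation, but neither SpO2 nor heart rate.

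**The concern.** The median over a short attempt starts from the infant's own pre-attempt level. Infants who start at different saturations may differ during the attempt for that reason alone, whatever the treatment does. The SAP accepts this for desaturation, which it measures against baseline. For the continuous level of the same signal it does not use the starting value.

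Two things are at stake. If baseline predicts outcome within strata, leaving it out makes the interval wider than it need be. And if the arms happen to differ at baseline, part of that difference appears in the treatment estimate, with nothing in Table 1 to warn the reader.

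These two medians deserve an efficient analysis because they are the only continuous SpO2 and heart-rate outcomes that use all first attempts. Time to and duration of desaturation or bradycardia, and duration of SpO2 above 97%, are each restricted to attempts in which the event occurred.

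**Working it through.** **Inputs from the SAP.** Section 11: 30% versus 50%, two-sided alpha 0.05, power 90%, 123 episodes per group (246 in total). Section 10: 1:1 allocation. The SAP gives no sample size, SD or correlation for the two medians.

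**The plan's own figure.** With pooled variance and no continuity correction, n per group = [1.96 × √(2 × 0.4 × 0.6) + 1.2816 × √(0.3 × 0.7 + 0.5 × 0.5)]² / 0.20² = (1.358 + 0.869)² / 0.04 ≈ 124. Power at 123 per group is 89.8%. The stated 123 is reproduced to within one episode per group and is used below.

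**Assumptions.** r is the within-stratum correlation between the pre-attempt value and the median during the attempt; it is assumed, and a range is shown. The model is linear, the SDs are equal, and all 246 episodes contribute.

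**Precision.** Adjustment multiplies the residual variance by 1 − r² and the interval width by √(1 − r²). The adjusted analysis of 246 episodes is worth an unadjusted one of 246 / (1 − r²).

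**Chance imbalance.** The standard error of the baseline difference is √(2/123) = 0.128 SD, so an imbalance of 1.96 standard errors is 0.25 SD. It moves the unadjusted estimate by r × 0.25 SD. Given a standardised imbalance b and no treatment effect, the unadjusted test statistic has mean r × b and SD √(1 − r²). The chance that the 95% interval excludes zero is therefore 1 − Φ[(1.96 − rb)/√(1 − r²)] + Φ[(−1.96 − rb)/√(1 − r²)].

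| Assumed r | Variance ratio | Width ratio | Worth (episodes) | Shift if imbalance is 0.25 SD | Interval excludes zero, b = 1.96 | Same, b = 1 |
|---|---|---|---|---|---|---|
| 0.2 | 0.96 | 0.98 | 256 | 0.05 SD | 6.3% | 5.0% |
| 0.5 | 0.75 | 0.87 | 328 | 0.125 SD | 12.9% | 4.8% |
| 0.7 | 0.51 | 0.71 | 482 | 0.175 SD | 20.5% | 3.9% |

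The last two columns are conditional on the imbalance. An imbalance of 1.96 standard errors or more, in either direction, arises in about 1 trial in 20. At an imbalance of one standard error the rate is not above 5%.

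**Is the covariate available?** For SpO2, yes: the desaturation score needs a baseline in each episode. For heart rate the SAP defines no baseline, since bradycardia is an absolute threshold of 100 beats per minute. Section 20 names bradycardia at randomisation as an exclusion, so heart rate is assessed then. That the oximetry recording also holds it is likely, but is an assumption here.

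**The case against.** The strongest reply is that nothing here is wrong. A stratum-adjusted comparison is unbiased over randomisations, its interval already allows for chance imbalance, and its error rate is 5%. Section 17 reports secondary outcomes only as estimates with unadjusted intervals, so no formal conclusion rests on them. The gain depends on a correlation that the SAP does not give; at r = 0.2 it is negligible. The 1 − r² rule belongs to linear models, while Section 27 may use quantile regression. All of this stands, and it limits the point to efficiency and transparency.

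The objection also bears on the remedy. The SpO2 baseline in the Definitions is read after randomisation in an unblinded trial. If flow had already started, adjusting for that reading could remove part of the treatment effect. A time point tied to placing the prongs would have no counterpart in the control arm. Filling in missing readings would sit badly with Section 28, which rules out imputing missing physiological data.

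Some stronger readings are tempting but not supported:

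- *The planned estimate is biased or its interval invalid.* It is neither; the higher rates in the table hold only given a large imbalance.
- *These are the trial's only unconditional physiological measures.* Section 26 counts incidence over all first attempts, so desaturation and bradycardia incidence are also unconditional. They are binary, and desaturation is already scored against the infant's own baseline.
- *A baseline is defined for both signals.* The SAP defines one for SpO2 only.

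**Conclusion.** The point holds as a specific, inexpensive improvement to two secondary analyses. The SAP compares raw levels, adjusts only for the stratification factors, and nowhere else supplies the missing adjustment, although it requires a pre-attempt SpO2 for another purpose. The cost is an interval wider than necessary, and a chance imbalance that enters the estimate unseen. If r is moderate, about 0.5, adjustment narrows the interval by some 13%; over r from 0.2 to 0.7 the range is about 2% to 29%. These figures rest on the assumed r, a linear model and complete data, and are only a guide for quantile regression. The primary outcome and its analysis are not affected.

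**What to change.** - **Covariates.** In the model for median SpO2, add pre-attempt SpO2 to the stratification factors. Define a pre-attempt heart rate from the same recording and add it to the model for median heart rate.
- **Time point.** Use one time point common to both arms that cannot carry a treatment effect, for example the last recorded value at or before randomisation. The value immediately before laryngoscope insertion is suitable only if flow has not yet started. An earlier reading may correlate less with the outcome, and the SAP does not say when recording begins; check this before choosing.
- **Table 1.** Report both baselines by arm.
- **Missing readings.** State a rule that fits Section 28: complete cases for these two models, or an explicit exception for baseline covariates. The wording needs care, because the last sentence of Section 28 leaves multiple imputation open in general.

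The cost is a wording change, one covariate per model, a small extra extraction from the recordings, and a few episodes without a baseline reading. It should be specified before the outcome data are analysed; if that has passed, label the adjusted result as post hoc.
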